### Data management

All research staff will receive training on data collection and other protocols, and the trial manager will monitor the quality of data collection by accompanying each researcher on some home visits during the study.

Data will be managed in accordance with Queen’s Standard Operating Procedure (SOP) for the management of data, in particular, electronic data. Available through *Queen’s On-line*, this SOP details how data are to be captured, in particular, with the informed consent of the research participant and giving details as to the purpose for which the information is to be used, the period of time it is to be retained and to whom it is likely to be disclosed. It is ICH GCP 1996 compliant. A study database will be established that is designed to ensure completeness, accuracy, reliability and consistency.

To ensure quality, all data will be double entered and a percentage of completed forms will be reviewed by the person responsible for data entry. Prior to data entry, each case report form will be checked for incomplete or missing information and any inconsistencies checked with the relevant researcher. A record will be kept of all queries raised and the response received.

Efforts will be made to obtain outcome measures from all participants enrolled in the trial, including any who withdraw from the study after randomisation.

### Data analyses

#### Analysis of process and qualitative data

Characteristics of participants recruited to each arm will be collected at baseline and used to assess patterns of attrition and the extent to which attrition rates appear to be associated with either arm of the trial. Data collected will include demographic data (e.g. age, ethnicity, marital status) and social complexities present. We will record details of women who decline to participate and use these data and those data available on NIMATS/CHS of those approached and those recruited, using age, parity and reasons for social complexity (where recorded, e.g. domestic violence, substance misuse, mental health problems).

The uptake rate of women agreeing to the intervention will be based on an assessment of the ratio of women randomised to the intervention group who then meet with the NBP health visitor on at least one occasion, relative to those who agree to take part in the trial and are randomised to NBP but do not attend the first (or any subsequent) meeting. The attrition rate will be calculated on the basis of the percentage of women who drop out relative to those who continue in either randomised group, together with those who subsequently decline to meet with their health visitor, irrespective of whether or not they continue to meet with the study researchers. Analyses of retention and compliance rate will inform estimates of likelihood of adverse events (e.g. withdrawal from the study), which will be important in designing the phase 3 RCT.

Whilst the sample size in this pilot study is not sufficient to inform the power calculations that will be required for a phase 3 study, we will use the available data to estimate variability of the outcomes, as this will help inform those calculations (see NIHR guidance on feasibility studies). To this aim, we will report the statistics obtained, interval estimates (e.g. 95% confidence intervals) and other sample statistics that may help inform power calculations.

Treatment integrity will be assessed by means of the records completed by health visitors at every visit/contact, plus data from the semi-structured interviews conducted at the end of the study, with nurses and women participants.

All semi-structured interviews will, with the permission of participants, be digitally recorded and later transcribed and analysed thematically, using NVivo (a computer-aided qualitative data analyses package).

#### Analysis of outcome data

Demographic data will be presented for all participants enrolled in the trial. No significance tests will be conducted to explore baseline differences. For continuous variables, we will report the mean, standard deviation, median, range and number of observations. Categorical variables will be reported in numbers and percentages.

The unit of analysis will be the individual participant. All primary analyses will be conducted according to intention-to-treat principles, irrespective of participants’ exposure to the programme, e.g. irrespective of how many home visits were achieved. The research team will endeavour to secure outcome measures for all participants, including those that move out of the area, or who subsequently decline to accept the programme. Examination of missing data (both case and item) will be undertaken on outcome measures and covariates, and particular attention will be paid to differential attrition and the possible reasons for this.

In the event of marked differential attrition or large amounts of missing data, we will consider methods such as inverse probability weighting to account for this. Sensitivity analyses will be conducted for all primary outcomes. Minimally, these will explore the potential impact of outliers and of missing data and the impact on the results of excluding participants who do not receive the programme, for whatever reason (because intention-to-treat analyses may underestimate the potential efficacy of an intervention).

We will use multiple regression modelling, with appropriate generalised linear models (GLMs) to explore the impact of the intervention, adjusting for the outcome measures at baseline. A statistical analysis plan will be developed in advance of the completion of data collection. This will include a small number of secondary analyses that either test emerging hypotheses (for example, concerning the programme’s impact on particular subgroups of mothers) or explore the effect of dose or compliance. We will conduct these analyses as an aid to estimating interval estimates (e.g. 95% confidence intervals) and variability in outcomes, in particular, to estimate between- and within-group variability: this information will be useful in planning the phase 3 RCT.

We do not anticipate undertaking any subgroup analyses in this pilot trial. We will, however, use the pilot trial to assess the feasibility of recruiting different subgroups that might be particularly important for the analyses of the main trial. In the main trial, we would anticipate using subgroup analyses to explore the moderating effects of factors such as nature of social complexity (e.g. presence or absence of substance misuse; presence or absence of history of maltreatment) or family status (e.g. primaparous, multiparous; maternal age).

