### Participants

In total, we aim to recruit 50 women with socially complex circumstances presenting for antenatal care at the Ulster, Ards and Bangor Hospitals (County Down) in the South Eastern Health and Social Care Trust in Northern Ireland. Twenty-five women will be randomised to receive the New Baby Programme. The remaining 25 women will receive Universal Core Programme recommended in the Healthy Child Programme through midwifery and health visiting services. This is the routine package of care that will be offered to those who do not wish to take part in the randomised trial. We aim to recruit the target sample of 50 participants over a 10-month period (Fig. 1).

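### The sensitivity analysis that excludes women who did not receive the programme can only remove women from the New Baby Programme arm, so it is not a randomised comparison; a complier estimate would answer the same question

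*Protocol article*

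**What the plan says.** All of this is in the protocol article. Under Analysis of outcome data, the main rule is clear: "All primary analyses will be conducted according to intention-to-treat principles", whatever the exposure to the programme. Outcomes will also be sought from women who decline it. The section then adds: "Sensitivity analyses will be conducted for all primary outcomes". The minimum content of these includes "the impact on the results of excluding participants who do not receive the programme, for whatever reason". The reason given is that intention to treat may understate what the intervention can achieve.

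The design is two arms of equal planned size: "In total, we aim to recruit 50 women with socially complex circumstances"; "Twenty-five women will be randomised to receive the New Baby Programme"; "The remaining 25 women will receive Universal Core Programme" (Participants). Under Analysis of process and qualitative data, uptake is defined for the intervention arm only, as meeting the NBP health visitor at least once.

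On subgroups, Analysis of outcome data says that the statistical analysis plan will contain a few secondary analyses. These either test emerging hypotheses, with the programme's "impact on particular subgroups of mothers" as the example, or explore dose or compliance. The last paragraph of the same section says: "We do not anticipate undertaking any subgroup analyses in this pilot trial".

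**The concern.** Receipt of the programme is decided after randomisation and can be seen in one arm only. Women in the comparator arm who would not have engaged, had they been offered NBP, cannot be identified and stay in. The exclusion therefore compares engaged NBP women with a mixture of would-be engagers and non-engagers.

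The protocol makes a prognostic difference plausible. Its Background says that women who booked late or missed many antenatal appointments were more often experiencing domestic abuse, misusing substances or known to child protection services. Intervention outcome measures links substance misuse to insecure and disorganised attachment.

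The planned adjustment for baseline outcome values cannot repair this for the two main intervention measures, because Table 1 schedules the Strange Situation and the CARE-Index at 12 months only.

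At stake is a secondary estimate, offered as a better guide to efficacy than intention to treat, that may show a benefit where there is none. The protocol says that the pilot's statistics and intervals may help inform phase 3 calculations, and that the pilot should help show whether a full trial is justified.

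**Working it through.** **Inputs from the protocol.** 50 women, 25 per arm (Participants; 25 + 25 = 50, consistent). Exclusion applies to non-receivers of the programme; uptake means at least one NBP visit. The protocol states no effect size, SD, alpha, power or non-uptake rate, so there is no calculated figure to reproduce.

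**Assumptions.** Share of non-receivers *q* = 10% to 30%. Prognostic gap *d* = 0.25 to 1.0 SD, by which would-be non-receivers do worse without the programme. Unit SD within each type of woman. Complete outcome data. Two-sided 5% level.

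**1. Bias of the exclusion analysis.** Set the mean of would-be receivers to 0 and of would-be non-receivers to −*d*. With no programme effect:

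- NBP arm after exclusion: mean 0
- Comparator arm, nobody excluded: mean −*q d*
- Difference: *q d*, although the true effect is zero

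| *q* | *d* = 0.25 | *d* = 0.5 | *d* = 1.0 |
|---|---|---|---|
| 10% | 0.025 | 0.05 | 0.10 |
| 20% | 0.05 | 0.10 | 0.20 |
| 30% | 0.075 | 0.15 | 0.30 |

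Simulation at *q* = 20%, *d* = 0.5 gave 0.102 for exclusion and 0.003 for intention to treat. If non-receivers would have done better, the sign reverses.

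**2. Exclusion against the complier estimate.** The complier estimate is the intention-to-treat difference divided by the proportion of the NBP arm that received the programme. Simulated means, 20,000 trials, 25 per arm:

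| Scenario | Exclusion | Complier estimate | Exclusion rejection rate |
|---|---|---|---|
| *q* = 20%, *d* = 0.8, no effect | +0.157 | −0.01 | 7.9% |
| *q* = 30%, *d* = 1.0, no effect | +0.299 | −0.02 | 13.7% |
| *q* = 20%, *d* = 0.8, true effect in receivers 0.5 | 0.66 | 0.49 | not applicable |

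The third row agrees with arithmetic: 0.5 + 0.2 × 0.8 = 0.66.

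**3. Price in precision** (*q* = 20%, *d* = 0.8). Variance in a full arm is 1 + 0.2 × 0.8 × 0.8² = 1.10.

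- Exclusion: √(1/20 + 1.10/25) = 0.31
- Complier estimate: √(2 × 1.10/25) / 0.8 = 0.37, against about 0.38 simulated

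**4. Scale for comparison.** The standard error of the arm difference with all 50 women is √(1/25 + 1/25) = 0.283 SD, so the 95% half-width is 1.96 × 0.283 = 0.55 SD.

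**5. Subgroups.** The interaction standard error is √(4/n₁ + 4/n₂), with n₁ + n₂ = 50. The interaction detectable at 80% power is 2.80 times this.

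| Subgroup share | SE | 95% half-width | Detectable at 80% power |
|---|---|---|---|
| 50% | 0.566 | 1.11 | 1.58 |
| 30% | 0.617 | 1.21 | 1.73 |
| 20% | 0.707 | 1.39 | 1.98 |

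Power for an interaction of 0.5 SD is 14% at an even split and 11% at a 20% share.

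**The case against.** The strongest reply is that this is only a sensitivity analysis. A reader might infer that the trial's main effect estimates would be biased. The protocol does not support that: intention to treat governs every primary analysis, and outcomes are pursued in women who decline the programme. The pilot's formal primary outcomes are recruitment and retention. This reply stands and limits the point to a secondary result.

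Second, the size and direction rest on assumed inputs. This also stands. Every value in the bias table is smaller than the 0.55 SD half-width, and the direction would reverse if lower-need women were the ones to decline.

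Third, the complier estimate is not clearly more accurate in so small a trial. At *q* = 20%, *d* = 0.8, the root mean square error is √(0.16² + 0.31²) = 0.35 for exclusion and about 0.38 for the complier estimate. That is a fair caution against expecting precision. But a wide interval centred on the right quantity shows its uncertainty, whereas the exclusion interval conceals a bias of unknown size.

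Fourth, the protocol already allows analyses of dose or compliance, and the estimator could be left to the statistical analysis plan. But the exclusion itself is not left open: the protocol fixes it as part of the minimum set.

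Fifth, a reader might infer that the two subgroup statements cannot both be followed. They can. Subgroup impact is one example in an either/or list, and the later statement says only that none is anticipated. A plan with dose or compliance analyses alone would satisfy both.

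Last, nothing in the protocol ties the decision on a full trial, or a phase 3 target effect, to the exclusion result or a subgroup result. The protocol itself says that the sample is too small to inform phase 3 power calculations. The risk is one of misreading, not of a stated rule.

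**Conclusion.** The point holds in a limited form. The exclusion analysis is committed, acts on one arm only, and does not estimate the effect among receivers that motivates it. Under no true effect it is off by *q d*: about 0.025 to 0.30 SD for 10% to 30% non-receipt and a gap of 0.25 to 1.0 SD. It favours NBP if non-receivers would have done worse. These inputs are assumptions, and the SD scale does not carry over directly to the Strange Situation if attachment is analysed in categories. The one-sidedness of the exclusion does not depend on them.

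The subgroup point is secondary. It is a mismatch of wording, in which an example suggests tests that the protocol elsewhere does not expect to run. With 50 women, such a test would need an interaction of about 1.6 to 2.0 SD for 80% power.

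**What to change.** 1. In Analysis of outcome data, name a complier average causal effect as the analysis of efficacy among receivers. Use randomisation as the instrument for at least one NBP visit (the protocol's own uptake definition) and the same covariates as the main model. Report it with its 95% confidence interval beside the intention-to-treat estimate.
2. Drop the exclusion analysis, or keep it labelled as descriptive and without causal interpretation.
3. Delete subgroup impact as the example of an emerging hypothesis, and report only the numbers recruited in each subgroup of interest, in line with the section's last paragraph.

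The cost is wording and a short analysis. The needed data are already planned, since uptake is recorded and outcomes are sought from women who decline the programme. The complier interval is wider (simulated SD about 0.38 against 0.31 at 20% non-receipt). The estimate also assumes that allocation to NBP has no effect on women who never have a visit, which should be stated with the result.

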#### Analyses of economic data

The economic evaluation will explore the incremental cost-effectiveness of the NBP compared to Management as Usual (MAU) at the 12-month follow-up. Firstly, a total cost per case per parent-infant dyad will be calculated to allow for a mean cost per case per trial arm for the intervention and control group, with rates of significance of difference between arms. Secondly, cost-effectiveness will be measured in terms of health-related quality of life (EQ-5D-5L) to determine incremental costs per quality-adjusted life year. Non-parametric bootstrapping will be used to generate a distribution of mean costs and effects for the two trial arms and develop confidence intervals around the incremental cost-effectiveness ratio. This process will also generate acceptability curves to illustrate the uncertainty associated with the estimate of costs and effects combined and estimates of affordability given potentially different decision-maker cost thresholds. The probability that the NBP could be more cost-effective compared with MAU for a range of maximum monetary values will then be explored.

In the main trial, longer-term implications of NBP will be explored with data from the main trial extrapolated and supplemented with data from the literature using decision analytic modelling techniques. The pilot trial will assist in identifying potential impacts of NBP for mothers who experience social complexity and their infants.

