### Randomisation

Randomisation is overseen by the School of Nursing and Midwifery (SNM) at Queen’s University, Belfast. It will use a central computer randomisation service (TENALEA) which employs a simple randomisation design in order to maintain complete randomness of the assignment of participants to either the intervention or comparator group.

Having secured written consent from a participant, the researcher will, on return to the office, enter the necessary details into TENALEA. The researcher will be provided with a unique study identifier for the participant but (in order to maintain the blinding of the researcher) not the random allocation. The random allocation will be conveyed by email from TENALEA to a designated officer in the School of Nursing and Midwifery for relaying to the relevant staff in the South Eastern Trust.

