Overall, response cards will be used for questions that provide a number of response options. All data will be collected during face-to-face interviews in the woman’s home, unless otherwise requested. In the event of respondents having low levels of literacy, the researcher will administer questions orally.

Outcome measures targeted by the intervention will be collected at baseline and 2, 6 and 12 months. Whilst the sample size in this pilot study is not sufficient to inform the power calculations that will be required for a phase 3 study, we will use the available data to estimate the standard deviation and interval estimates (i.e. 95% confidence intervals) of the outcome measures, as this will help inform those calculations (see NIHR guidance on feasibility studies).

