### Economic evaluation

Economic data, including resource use and unit costs, will be collected in parallel with the trial. Resource use information will be derived at the individual level from parental self-report on use of local resources and health and social services. A resource measurement tool designed and standardised for the group Nurse-Family Partnership study will be used. Health visitors delivering the intervention will record the time spent and activities undertaken in support of the parent-infant dyad.

NBP costs will be calculated using a standard micro-costing (bottom-up) approach and will be based on health visitor salaries plus on-costs (employers’ national insurance and superannuation contributions) and appropriate capital, administration and training costs. Nationally applicable unit costs will be applied to all community health and social care contacts, derived from the Personal Social Services Research Unit (PSSRU), and medications, derived from the British National Formulary. Costs for NHS hospital contacts will be taken from NHS reference costs.

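### With about 25 women per arm, the planned confidence interval around the ICER will usually have no ordered meaning and the planned cost significance test has little power; report incremental cost, QALYs and net benefit with intervals instead

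*Protocol article*

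**What the plan says.** The section Analyses of economic data sets out two steps. The first is a mean cost per case in each arm, reported "with rates of significance of difference between arms". The second is an incremental cost per QALY based on EQ-5D-5L, with a non-parametric bootstrap of arm mean costs and effects used to "develop confidence intervals around the incremental cost-effectiveness ratio". The same bootstrap feeds acceptability curves and the probability of cost-effectiveness over a range of monetary thresholds.

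On size, the Participants section says "In total, we aim to recruit 50 women with socially complex circumstances". It adds "Twenty-five women will be randomised to receive the New Baby Programme" and "The remaining 25 women will receive Universal Core Programme". Under Randomisation, the service "employs a simple randomisation design in order to maintain complete randomness of the assignment of participants", so neither arm sizes nor baseline utility are balanced by design.

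Table 1 schedules EQ-5D-5L at baseline and at 2, 6 and 12 months. Under Intervention outcome measures the article says that "the sample size in this pilot study is not sufficient to inform the power calculations" needed for phase 3. It goes on to say that the data will still be used to estimate standard deviations and 95% confidence intervals to help inform those calculations.

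**The concern.** An ICER is a ratio of two estimated differences. When the QALY difference can take either sign, the ratio loses its order. With illustrative figures of 1500 for cost and 0.02 for QALYs:

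- costlier and worse: 1500 / (−0.02) = −75,000 (dominated)
- cheaper and better: (−1500) / 0.02 = −75,000 (dominant)
- costlier and better: 1500 / 0.02 = +75,000
- cheaper and worse: (−1500) / (−0.02) = +75,000

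One number therefore carries opposite meanings. Near zero the ratio jumps: 1500 / 0.001 = 1,500,000, but 1500 / (−0.001) = −1,500,000. Sorting such replicates and taking the 2.5th and 97.5th percentiles does not bound anything.

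The cost test raises a separate worry. A non-significant result from so few women is likely whether or not the programme changes cost, and it can be misread as showing no difference. The Discussion wants the pilot to indicate whether a full trial is justified, and the economic section expects it to help identify potential impacts. A disordered interval or a non-significant cost test could mislead a reader on both.

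**Working it through.** **What can be reproduced.** Only the arm sizes: 25 + 25 = 50. The article gives no alpha, power, QALY SD, cost SD, expected difference or dropout for the economic analysis. Everything below therefore assumes two-sided 5%, QALY SD 0.10 to 0.25, a true QALY difference of 0 to 0.05, and 20 to 25 women analysed per arm.

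**Precision.** SE of a difference = SD × √(2/n). At n = 25 this is SD × √0.08 = 0.283 SD, so the 95% half-width is 1.96 × 0.283 = 0.55 SD. At n = 20 the figures are 0.316 SD and 0.62 SD.

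**How often the QALY interval covers zero.** With z = d/SE, P = 1 − [Φ(z − 1.96) + Φ(−z − 1.96)]. Example: d = 0.05 and SD = 0.10 give SE = 0.0283, z = 1.77 and P = 0.576. At 25 per arm:

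| True difference | SD 0.10 | SD 0.15 | SD 0.20 | SD 0.25 |
|---|---|---|---|---|
| 0 | 0.950 | 0.950 | 0.950 | 0.950 |
| 0.02 | 0.891 | 0.924 | 0.936 | 0.941 |
| 0.03 | 0.815 | 0.891 | 0.917 | 0.929 |
| 0.05 | 0.576 | 0.782 | 0.857 | 0.891 |

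At 20 per arm the range is 0.647 to 0.950.

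**Bootstrap check.** In 400 simulated trials of 1,000 resamples each, with normal QALYs, SD 0.10 and 0.20 and 25 per arm, the share of trials with more than 2.5% of bootstrap QALY differences on each side of zero ran from 0.555 (difference 0.05, SD 0.10) to 0.950 (difference 0, SD 0.20). That is the condition under which percentile ICER limits lose their order.

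**Would another interval method rescue the ratio?** Fieller's set contains the ratios R with (ΔC − RΔE)² ≤ 1.96² × var(ΔC − RΔE). It is a bounded interval only if the coefficient of R², ΔE² − 1.96² × var(ΔE), is positive. That is, the QALY difference must itself be significant, so the table applies to this method as well.

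**Cost test.** Power ≈ Φ(δ/0.283 − 1.96), with δ in SD units:

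- δ = 0.3: Φ(1.06 − 1.96) = 0.184
- δ = 0.5: Φ(1.77 − 1.96) = 0.424

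For 80% power the needed size is 2 × (2.80/δ)², or 175 per arm for 0.3 SD and 63 per arm for 0.5 SD. With 25 per arm, 80% power is reached only at 2.80 × 0.283 = 0.79 SD. This is a normal approximation, and skewed costs would change the figures somewhat.

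**What baseline adjustment adds.** With baseline-to-QALY correlation ρ, the SE is multiplied by √(1 − ρ²): 0.866 at ρ = 0.5 (13% lower) and 0.714 at ρ = 0.7 (29% lower). Both correlations are assumed. For d = 0.03 and SD 0.20, the chance that the QALY interval covers zero goes from 0.917 to 0.906 or 0.885. In the most favourable cell (d = 0.05, SD 0.10) it goes from 0.576 to 0.468 or 0.303.

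**Chance baseline imbalance.** For an assumed utility SD of 0.15 to 0.30 at 25 per arm, the SE of the baseline difference is 0.042 to 0.085. The chance of a gap above 0.05 in either direction is 24% to 56%.

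**The case against.** The strongest reply is that this is an exploratory analysis. The economic section speaks of exploring cost-effectiveness, the evaluation is not among the listed primary or secondary outcomes, and no passage makes the ICER a progression or commissioning criterion. The article is open about its small sample. It also already plans acceptability curves, which count the share of replicates with positive net benefit at each threshold and so need no stable ratio. All of this stands, and it limits the weight of the point. It does not give an order to the limits of an ICER interval that the article explicitly plans, nor does it supply a reason for a cost test.

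Three stronger readings are tempting, and the article does not support them.

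- **The analysis is planned as unadjusted.** A reader might infer this from the bootstrap of arm means. The section is silent on covariates, and adjusted means fit its wording. Analysis of outcome data commits to adjustment for baseline outcome measures, although it does not expressly govern the economic section. Covariates may be left to the analysis plan, which is not shown. Nor would lack of adjustment be the cause: small numbers and a near-zero denominator are.
- **All the economic results are uninterpretable.** The curves and the joint distribution remain readable, only very imprecise.
- **Programme visits are counted twice.** A reader might infer this because parents report service use while "Health visitors delivering the intervention will record the time spent and activities undertaken in support of the parent-infant dyad". Nothing says that the same visits will enter the total from both sources.

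The remark about power calculations should also not be stretched. It concerns planning phase 3 and does not mention costs.

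**Conclusion.** The point holds for two stated choices: the interval around the ICER and the significance result on mean cost. With about 25 women per arm, the QALY difference straddles zero in roughly 56% to 95% of pilots under the assumed SDs and gains. Even at the favourable end, the ICER interval fails more often than not. The cost test would miss a 0.5 SD difference more often than it finds it, and it sits awkwardly beside a protocol that elsewhere justifies its analyses as estimating intervals and variability.

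The size of the problem rests on assumed SDs and effects, because the article gives none. A much larger QALY gain or a much smaller SD would weaken the ratio argument. Adjustment for baseline utility is worth having but secondary. This is a cheap improvement to an exploratory analysis and does not threaten the pilot's feasibility aims.

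**What to change.** In Analyses of economic data, or in the analysis plan that the article says will be written before data collection ends:

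1. Replace the ICER interval with incremental cost, incremental QALYs and incremental net monetary benefit (threshold × QALY difference − cost difference), each with a 95% CI. Give net benefit at the thresholds already planned for the acceptability curves, and show the cost-effectiveness plane. Net benefit is linear in both differences, so its bootstrap limits keep their order.
2. Replace the significance result on costs with the mean difference and its 95% CI.
3. Label all of these results as exploratory.
4. As a secondary gain, estimate QALYs within each bootstrap replicate by regression on arm and baseline EQ-5D-5L. This matches the baseline adjustment stated for the outcome models, adds some precision and deals with chance baseline imbalance.

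The cost is a few lines of analysis code and some wording. The bootstrap, the threshold range and the baseline EQ-5D-5L are already planned, and no new data are needed.
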